#### Primary data

##### Pre-post patient survey

The patient survey will be conducted in n = 50 randomly selected intervention GP practices that will be drawn from the population of n = 1057 GPs of the intervention group, stratified by ASHIP. The selected practices will receive the study materials for the two patient surveys pre and post implementation. The recruitment of patients will be done by the practice staff. Patients will be asked to complete an anonymous, paper-based questionnaire after their consultation with the GP. The questionnaires will be handed out in sealed envelopes and can be completed in the GP practice or at home. For the pre-implementation survey, patients who visited the GP practice in the 4–8 weeks before the intervention starts will be recruited. For the post-implementation survey, patients who visit the GP practice in the end of the intervention will be recruited. Each of the GP practices participating in the patient survey is asked to recruit a minimum of n = 25 patients for each survey round (2x n = 1250 patients). To increase the response, the practices receive a material incentive in the form of a gift box after n = 10 questionnaires and for all further questionnaires a financial incentive of 5 € per questionnaire.

##### Online survey of GPs and medical assistants

The recruitment for the online survey of GPs and medical assistants in all intervention practices (n = 1057 GPs and n = 1057 medical assistants) takes place via a postal letter to the GPs and the medical assistants. The cover letter contains a QR code to the online survey. To increase the response, a financial incentive (25 € per completed online survey) and other methods (e.g., 2 waves of reminders, personalised cover letters, university logo) are planned [34–36]. Based on previous experience from a similar project, a response of 66% (n = 698 GPs and n = 698 medical assistants) can be assumed.

##### Qualitative interviews with patients, GPs, and medical assistants

For the individual interviews, GPs and medical assistants in the participating GP practices will be recruited by telephone by the research team using purposeful sampling [37] (by gender, age, region, and individual vs. joint practice). GPs and medical assistants will be recruited preferably from the 50 intervention practices participating in the patient survey to enable integrated analyses of quantitative and qualitative data from the same practices. The recruited GPs and medical assistants will receive information on the study and consent forms in advance. The interviews can take place in the GP practice, at a location of their choice, or by telephone and will be audio-recorded. For the interview, which will last up to 60 min, a financial incentive is planned (50 € per interview).

For the patient interviews, participants will be recruited via the participating intervention practices (n = 50) using purposeful sampling (by gender, age, and region). The intervention GP practices will approach potential interview participants and will invite them to participate in the interview study. The research team will contact the patients and will arrange an interview appointment. The interviews will be conducted by the research team in the patients’ homes, at a location of their choice, or by telephone, and will be audio-recorded.

The estimated number of interviews in the three groups aligns with the recommendation of 20 to 30 interviews per interviewed group suggested by Flick et al. [38]. Accordingly, 30 interviews with patients, 20 interviews with GPs, and 20 interviews with medical assistants are planned. The higher number of interviews with patients is due to the fact that a higher heterogeneity, e.g., in terms of socio-demographic characteristics is expected. Flick [39] advocates the number of cases mentioned in order to obtain manageable and useful data.

### Measures

#### Secondary data collection

The influenza vaccination rate as primary outcome is measured annually for patients insured by a substitute health insurance fund aged 60 and older. The rate will be computed as the fraction of the amount of vaccinated patients insured by a substitute health insurance fund aged 60 and older and all patients insured by a substitute health insurance fund aged 60 and older of the practice under consideration.

The determination of the secondary outcome, vaccination uptake rates for vaccinations recommended by the STIKO for patients aged 60 and older (except for influenza), is more challenging. This is due to the unclear size of the basic population, which, in turn, is a result of the long periods of time between recommended booster vaccinations (the boosters for tetanus, diphtheria, and pertussis are needed/recommended only every 10 years).

If a sufficiently high number of cases is reached, subgroup analyses for different vaccinations are planned (e.g., for pneumococci and herpes zoster).

#### Primary data collection

In the pre-post patient survey, the secondary outcome vaccine literacy and further constructs such as general health literacy, psychological antecedents of vaccination behaviour, intention to get vaccinated, knowledge about vaccination, as well as numerous confounders and sociodemographic information will be assessed. The outcome vaccine literacy is assessed using the validated subscale of the Health Literacy Population Survey Project 2019–2021 (HLS19) instrument (HLS19-VAC-DE) [40]. General health literacy is measured with the generic short version of the instrument for measuring health literacy in the general population (HLS19-Q12; [40]. Psychological antecedents of vaccination behaviour are surveyed with the short version of the associated validated 5 C scale [18, 41]. The intention to get vaccinated is surveyed in a vaccine-specific manner using the item from the study by Betsch et al. [42].

Knowledge about influenza and pneumococci vaccination is assessed using an instrument based on the validated scale developed by Zingg & Siegrist [43]. (Un)met information needs regarding vaccination are assessed with items based on an instrument developed by Neumann et al. [44]. In addition to the listed central constructs, possible moderators such as the GPs’ empathy (Consultation and Relational Empathy scale) [45, 46] and trust in the GPs and medical assistants [47] are also included in the questionnaire. Furthermore, patient experiences regarding communication with the practice staff are surveyed. These include aspects such as carrying out a vaccination check, reminding, answering questions regarding vaccinations, and distributing written information. Sociodemographic variables (e.g., age, gender, employment) will be collected at both time points (pre and post implementation), as this is an anonymous survey with independent patient populations.

The focus of the online survey of GPs and medical assistants is on their experiences with and evaluation of the intervention. These aspects will be assessed with both self-developed instruments and validated instruments. For assessing the self-reported communication competence, the validated scale Medical Communication Competence Scale [48] is used. Furthermore, the online survey will include questions on structural characteristics of the GP practices such as size and type of the practice as well as sociodemographic characteristics of the GPs and the medical assistants (e.g., age, gender).

For the formative evaluation, guideline-based, semi-structured interviews with GPs, medical assistants, and patients will be conducted. In the interviews, patients will be asked about their vaccine literacy, their attitudes toward vaccination, their knowledge about vaccination, and their experiences regarding vaccine-related communication with the GP and the medical assistant (see Fig. 2). In the interviews, the GPs and medical assistants will mainly be asked about their experiences with the intervention and their vaccine-related communication with the patients.

**Table 1 Tab1:** Data collection methods for the summative and formative evaluation

Data collection methods and timepoints	Indicators to be measured	Measurement instruments	Data analysis
***Summative evaluation (secondary and primary data)***			
**Secondary data**: Extract of pseudonymised contract GP billing data according to § 295 SGB V, n = 2114 GPs (n = 1057 GPs each in the intervention and control group) and at full utilisation ≥ 147,980 patients	**Primary outcome**: Influenza vaccination rate **Secondary outcome**: Vaccination uptake rate of the vaccinations recommended by the STIKO for patients aged 60 and older (except for influenza)	-	Descriptive statistics, pre-post comparison (intervention/control group), cluster analysis, subgroup analyses
**Primary data**: Cross-sectional patient survey in intervention practices (n = 50), pre- and post-implementation (2 x n = 1250 patients), paper & pencil survey	**Secondary outcome**: Vaccine literacy	**Further secondary outcome**: HLS19-VAC-DE subscale of the HLS19 instrument (40)	Descriptive statistics, multivariable regression models, multilevel analysis

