Thus, it is assumed in the following that the influenza vaccination uptake rate as primary outcome increases by 3% as a result of the intervention. This 3%-increase should be seen as an initial change. To detect this effect in the secondary data analysis with a power of 90% at a significance level of alpha = 5% (two-sided), 17,508 patients would be needed without considering the cluster effect. Based on available anonymised data from previous studies [32, 33], the intra-cluster correlation (ICC) is expected to be 0.08. With a mean cluster size of 48 patients per practice vaccinated against influenza on average, this results in a design effect of 4.76 and a corresponding required case number of 83,338 patients. Accordingly, about 1736 GPs would be needed (868 GPs in the intervention and control groups each). Likewise, an increase of 3% is also targeted for increase in vaccination uptake rate of further recommended vaccinations as the secondary outcomes. Since the assumed cluster size is reduced to 28, resulting in a design effect of 3.16 with an ICC of 0.08, a case number of 55,325 patients is required for these analyses. For this, 1976 GPs are needed according to the cluster size – 988 GPs in each of the intervention and control groups. Therefore, due to the smaller cluster size for the secondary outcome, a total of 988 GPs is required for the intervention group for the analysis. To ensure that the required number of cases will be achieved, an additional 7% (69 GPs) was added to the calculated number of cases. This resulted in a required total number of 1057 GPs per group.

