### Recruitment

The recruitment of GPs for study participation takes place three months prior to the start of the intervention phase by the three participating regional Associations of Statutory Health Insurance Physicians (ASHIP) Schleswig-Holstein, North Rhine and Westphalia-Lippe, considering the available contingent of participants in their region. In Germany, the ASHIP are bodies under public law, which represent all physicians and psychotherapists treating compulsory insured patients. First, all potentially eligible GPs in the three regions, meaning GPs participating in primary care according to § 73 (1a) SGB V (excluding paediatricians), who have vaccinated patients aged 60 and older insured by the substitute health insurance fund in the past, will be identified. Substitute health insurance funds are a type of health insurance fund with the largest percentage of insured persons on the German market. There are no other major differences between this and other types of health insurance funds. Subsequently, these GPs will be stratified by the three ASHIPs, and randomised into two groups (intervention/control). The potential participating GPs in the intervention group will be contacted by the responsible ASHIP and receive the offer to participate in the intervention group. It is pointed out that participation in the intervention is also associated with participation in the accompanying evaluation study. Subsequently, all enrolled GPs, as well as at least one medical assistant from the practice, complete the online training that is completed after an online knowledge test and submit the certificate of successful participation to the associated ASHIP.

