#### Secondary data

After submitting the certificate and vaccinating at least 20 patients aged 60 and older insured by a substitute health insurance fund in the first quarter of evaluation, the GP will receive an initial starter lump sum payment. Through this lump sum payment, the GP is marked as a participant in the billing data of the ASHIP and is available in a pseudonymised form for the summative evaluation over all quarters considered. Since secondary data (extract of pseudonymised contractual GP billing data according to § 295 SGB V) is used, the relevant data is available for both the intervention and the control group.

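### The control group is carried over as 1057 GPs although all eligible GPs are randomised and control billing data need no enrolment; the plan should say that all randomised controls are analysed

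*Protocol article*

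**What the plan says.** Four parts of the protocol article bear on who the controls are.

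- **Recruitment.** All potentially eligible GPs in the three regions are identified first. Then: "Subsequently, these GPs will be stratified by the three ASHIPs, and randomised into two groups (intervention/control"). Only GPs allocated to the intervention are contacted, decide whether to accept, and complete the training with a medical assistant.
- **Recruitment, Secondary data.** An intervention GP is marked as a participant in the billing data through a starter payment, made after the training certificate is submitted and at least 20 patients of the target group are vaccinated. No enrolment step is described for controls, because routine billing data are used and "the relevant data is available for both the intervention and the control group".
- **Sample and Table 1.** The Sample section ends with "This resulted in a required total number of 1057 GPs per group". Table 1 repeats this for the billing-data analysis: "n = 2114 GPs (n = 1057 GPs each in the intervention and control group").
- **Summative evaluation: secondary data.** The research questions compare intervention and control groups. For the vaccinations other than influenza, however, the text contrasts GPs who take part with GPs who do not.

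The number of eligible GPs, the allocation ratio and the expected participation rate are not given.

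**The concern.** The figure of 1057 is a recruitment target. It makes sense for the intervention group, where each GP has to be won over. It has no such meaning for the control group, where every randomised GP already generates the outcome data. With equal allocation, the randomised control group numbers exactly 1057 only if every invited intervention GP accepts and qualifies. In any other case it is larger, and Table 1 then describes fewer controls than the design produces.

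Two things are at stake. The first is precision that costs almost nothing to keep. The second is the identity of the comparator. As written, it could be all randomised controls, 1057 of them, or all GPs who do not take part. The third set may include GPs who were randomised to the intervention and declined, so it would no longer be the group formed by randomisation.

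**Working it through.** **Inputs from the Sample section.** 17,508 patients before clustering, 90% power, two-sided alpha 5%, ICC 0.08, mean cluster size m = 48 (influenza) and m = 28 (other vaccinations), 7% reserve.

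**Assumptions (not in the article).** Allocation 1:1. A share r of the GPs randomised to the intervention joins and qualifies, with r between 0.1 and 0.5. Cluster size and ICC are the same in both groups.

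**1. The plan's own figure.**
- Influenza: design effect 1 + 47 × 0.08 = 4.76; 17,508 × 4.76 = 83,338; 83,338 / 48 = 1736 GPs, or 868 per group.
- Other vaccinations: design effect 1 + 27 × 0.08 = 3.16; 17,508 × 3.16 = 55,325; 55,325 / 28 = 1976 GPs, or 988 per group.
- Reserve: 988 × 1.07 = 1057 per group, 2114 in total.

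The figure reproduces from 17,508 onward, and it is the result of a 1:1 calculation.

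**2. Size of the randomised control group.** With 1057 participating intervention GPs and 1:1 allocation, controls number 1057 / r.

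**3. Standard error with all controls, relative to 1057 controls.** The ratio is sqrt[(1/1057 + r/1057) / (2/1057)] = sqrt[(1 + r)/2].

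| r | Controls | SE ratio | Reduction |
|---|---|---|---|
| 0.5 | 2114 | 0.866 | 13% |
| 0.3 | 3523 | 0.806 | 19% |
| 0.2 | 5285 | 0.775 | 23% |
| 0.1 | 10,570 | 0.742 | 26% |

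The ceiling, with unlimited controls, is 1 − sqrt(0.5) = 29%.

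For scale, take the 47.3% influenza rate from the Background as an assumed baseline, with m = 48. The standard error of the difference is sqrt[0.473 × 0.527 × 4.76 × 2/(1057 × 48)] = 0.68 percentage points with 1057 controls and 0.59 with 2114. The 95% half-widths are 1.96 × 0.684 = 1.34 and 1.96 × 0.592 = 1.16 points.

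**4. Power, calibrated to the article's own number.** Take 17,508 independent patients at 1:1 as giving 90% power. The expected test statistic is then 1.96 + 1.2816 = 3.2415, at 8754 patients per group. For n_I intervention and n_C control GPs it becomes 3.2415 × sqrt{ [1/(1/n_I + 1/n_C)] × (m/DE) / 4377 }, and power is Φ(that value − 1.96).

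- 1057 vs 1057, m = 48: 1057 × 48/4.76 = 10,659 effective patients per group; 3.2415 × sqrt(10,659/8754) = 3.577; power 94.7%.
- 1057 vs 1057, m = 28: 1057 × 28/3.16 = 9366; 3.2415 × sqrt(9366/8754) = 3.353; power 91.8%.
- 1057 vs 2114: 98.5% (m = 48) and 97.2% (m = 28).
- Recruitment shortfall, 528 intervention GPs, m = 28: 78.1% with 1057 controls, 85.0% with 2114, 87.4% with 3171.
- The same shortfall with m = 48: 83.1%, 89.2% and 91.2%.

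**5. All GPs as randomised in both groups.** This is a different comparison. If GPs who decline show no effect, the effect shrinks by the factor r. With 3 absolute points, a 47.3% baseline, m = 48 and r = 0.5, there are 2114 GPs per group and the effect is 1.5 points. The standard error is 0.684/sqrt(2) = 0.484 points, and power is Φ(1.5/0.484 − 1.96) = 87%. On the same inputs, an undiluted 3 points with 1057 per group gives 99%.

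**The case against.** **The article states no cap.** The Sample section calls 1057 a required number, and Table 1 places it beside a patient count worded as a minimum (147,980 = 70 × 2114). A reader might infer that surplus controls will be discarded. No sentence says so, and 1057 can be read as a floor. This stands, and it is why the point is to state the rule, not to allege that data are thrown away.

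**The surplus is inferred.** This also stands: the pool, the ratio and the participation rate are all missing, so the gain is a conditional range. Still, under equal allocation there is no surplus only if every invited GP joins and qualifies.

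**A journal article may leave control sampling to the full protocol.** That is fair for the sampling mechanics. It does not explain why the article's own descriptions of the control group differ between the Recruitment section, Table 1 and the text on the other vaccinations.

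**Stronger readings that the documents do not support.**
- A reader might infer that using 1057 of a larger control group is biased in itself. A random subset of a randomised group remains a fair comparator, and nothing shows that the subset would be chosen otherwise.
- A reader might infer that extra controls repair the self-selection of intervention GPs. They do not: acceptance, training and the 20-patient condition still act on one side only.
- A reader might take the 3% as relative to 47.3% and conclude that the trial is badly underpowered without more controls. That reading needs about 52,000 patients before clustering, which does not fit "17,508 patients would be needed without considering the cluster effect".

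**Conclusion.** The point holds as a near-free improvement in precision combined with an inconsistency over who the controls are. Under 1:1 allocation and r from 0.5 down to 0.1, using all randomised controls reduces the standard error by 13% to 26%, provided the intervention side stays at 1057 GPs.

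The trial does not depend on this to reach its power target at full recruitment: 94.7% and 91.8% on its own inputs, against a planned 90%. The gain lies in interval width, in the regional and single-vaccination analyses that the article makes conditional on sufficient case numbers, and in protection against an intervention shortfall. With half the intervention GPs, power for the other vaccinations is 78% with 1057 controls and 85% with 2114.

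The calibration takes 17,508 as given, because the article states no baseline rate for it.

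The wording about GPs who do not take part is the part most in need of correction for the vaccinations other than influenza, since it could move decliners from the intervention arm into the comparator.

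**What to change.** 1. In Table 1 and the Sample section, state that all GPs randomised to control who meet the same pre-randomisation eligibility rule as the intervention GPs are analysed, with 1057 as a minimum, and that the comparison is adjusted for regional association (the randomisation stratum). If a sample of controls is really intended, say so and give the sampling rule.
2. State the number of GPs randomised and the allocation ratio.
3. In Summative evaluation: secondary data, name the randomised control group as the comparator, so that GPs randomised to the intervention who declined are not counted as controls.
4. An analysis of all GPs randomised to the intervention can be reported alongside to address self-selection. Its price is dilution by r (87% against 99% power in the example at r = 0.5), so the precision gains above do not apply to it.

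The cost is a larger billing extract and a few sentences, with no extra recruitment. The extract must carry the randomised allocation, because the only marker the article describes is the participants' starter payment.

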***Formative evaluation (primary data only)***			
Cross-sectional patient survey in intervention practices (n = 50), pre- and post-implementation (2 x n = 1250 patients), paper & pencil survey	Attitudes towards vaccination; intention to get vaccinated; knowledge about vaccination; (un)met information needs; vaccination-related interaction between GP practice staff and patients	5 C instrument (18, 41); vaccination intention item (42); instrument based on the validated scale developed by Zingg & Siegrist (43) to measure knowledge about vaccination; instrument based on CaPts to measure (un)met information needs (44); self-developed items on vaccination-related interaction between GP practice staff and patients	Descriptive statistics, multivariable regression models, multilevel analysis
Cross-sectional online survey with GPs and medical assistants in intervention practices (n = 2 × 1057)	Experiences with and evaluation of the intervention elements, also in nursing homes and outpatient care, evaluation of changes in the GP-patient interaction; self-reported communication competence of GPs; structural information related to GP practices	Self-developed, best-fit instruments on experience with and assessment of the intervention; Medical Communication Competence Scale (MCCS; (48); self-developed items on structural information related to GP practices	Descriptive statistics, multilevel analysis after linkage with patient survey data, subgroup analyses
Qualitative interviews with patients in intervention GP practices, n = 30	Experiences with the intervention, subjective effectiveness	Semi-structured guideline	Structuring qualitative content analysis according to Kuckartz (49)
Qualitative interviews with GPs/medical assistants in intervention GP practices, n = 40	Experiences with the intervention, subjective effectiveness	Semi-structured guideline	Structuring qualitative content analysis according to Kuckartz (49)

